### Other outcomes

The relationship between the client and family carer during the past month will be assessed using the Dyadic Relationship Scale (DRS) [31].Costs associated with the training and support provided to HCWs, as well as health resource utilisation amongst clients, will be measured using the RUD Lite [13].

Health care-related service costs will be collected using Medicare Benefits Scheme and Pharmaceutical Benefits Scheme data and the RUD Lite [32]. Overall health status of clients will be assessed using EuroQol 5 Dimensions 5 Levels (EQ-5D-5L or EQ-5D-5L Proxy Version) [33] and the ICEpop CAPability measure for Older people (ICECAP-O) [34]. All-cause client transition from home will be collected from a variety of sources such as the case manager files, MBS and PBS data.

### Other data collection and routine data

Client cognition and functional performance will be assessed by the trained research team using the Rowland Universal Dementia Assessment Scale (RUDAS) at enrolment and is not an outcome measure (35). Relevant medical and care related documentation will also be collected from home care service providers.

### Qualitative measures

Additional free-text questions will assess the impact of COVID-19 on home care service delivery as well as provide context on the outcome measure collected. HCWs will be asked about the impact of the pandemic on their work practice and themselves personally. Clients and family carers will be asked about the impact of the pandemic on their needs, circumstances, and home care services provided to them.

## Trial schedule

### Informed consent and screening

The following section includes both the intended (and partially completed) procedures for the SW-CRT prior to the COVID-19 pandemic. The pandemic necessitated some changes to the procedures which are also described.

Pre-COVID-19 and post COVID-19, written informed consent is obtained from each participant (clients, family carers and HCWs) prior to participating in the study. This trial does not involve collecting biological specimens from participants for storage.

Research staff assess each client’s capacity to consent using the recommended approach by the Dementia Centre for Research Collaboration. If researchers are of the opinion that a client’s capacity is sufficiently impaired, a person responsible or a medical treatment decision-maker may provide consent on their behalf. This approach is considered less invasive than conducting a formal assessment with someone who may not have capacity to consent to the test or involving the potential participant’s medical practitioner. Clients, family carers, and HCWs are not substantially reimbursed for participating in the study. However, HCWs receive their usual pay to participate in the assessment visits and to attend PITCH training, whilst backfill will be arranged with the home care providers to cover HCWs’ usual duties during these times. Clients and family carers receive a $50 gift voucher at the end of period 3. All participants are informed they are free to withdraw from the study at any time. If a participant withdraws after the baseline measures are completed, then no replacement is made.

### Visits

Assessment visits are scheduled in period 1, 2, and 3: baseline, 6 months, and 12 months respectively. All participants will be assessed as outlined in Fig. 2.

Prior to the COVID-19 pandemic, client and family carer assessments were conducted face-to-face at the participant’s home, although, if preferable, participants could choose to be assessed at the lead organisation or at a study partner University. HCW assessments were also conducted face-to-face either in their home, at the lead organisation, or at the home care provider’s offices, as preferred by the HCWs. Due to the COVID-19 pandemic, assessment visits are now conducted remotely, to protect the health and safety of participants and researchers. During the pandemic, client and family carer assessments are conducted via telephone, and HCW assessments are conducted only via online questionnaires using the lead organisation’s survey platform (REDCap).

Prior to COVID-19, client and family carer face-to-face assessments took approximately 1 h each to complete. Similarly, client and family carer telephone assessments during the pandemic took approximately 1 h each. The cognitive screening assessment was modified for suitable use over the telephone. These include involving the family carer in administering the visuo-spatial orientation and visuo-constructional drawing tasks and the removal of the praxis task. Family carer telephone assessments remained unchanged.

Prior to COVID-19, HCW assessments took approximately 30 min to complete. During the pandemic, HCWs were able to complete assessments online.

At the start of the pandemic, additional questions regarding the impact of COVID-19 were added to the assessments for HCWs, clients, and family carers.

### Sample size

For the primary outcome measure (SCIDS), at 80% power, two-tailed 5% significance level, 12 clusters with 15 HCWs per cluster, will detect a treatment effect size of 0.522 in the treatment group compared with controls. With a 20% drop-out rate, sample size is estimated at 216 HCWs. All eligible clients serviced by these HCWs are invited to participate in the study (approximately 108 participants). The family carers of participating clients are also invited to participate in the study (approximately 108 participants).

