**Methods:**

This study is a pragmatic stepped-wedge cluster-randomised controlled trial (SW-CRT). Home care workers (HCWs) from seven home care service providers are grouped into 18 geographical clusters. Clusters are randomly assigned to intervention or control groups. The intervention group receives 7 h of a dementia education and upskilling programme (Promoting Independence Through quality dementia Care at Home [PITCH]) after baseline measures. The control group receives PITCH training 6 months after baseline measures. This approach will ensure that all participants are offered the program. Home care clients living with dementia are also invited to participate, as well as their family carers. The primary outcome measure is HCWs’ sense of competence in dementia care provision.

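### The 20% drop-out allowance is computed as 180 × 1.2 = 216 HCWs; keeping 180 after a 20% loss needs 180/0.8 = 225, a small error that a restatement corrects

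*Protocol article*

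**What the plan says.** The Sample size section of the protocol article sets the operating characteristics "at 80% power, two-tailed 5% significance level" and says that "12 clusters with 15 HCWs per cluster, will detect a treatment effect size of 0.522 in the treatment group compared with controls". The next sentence makes the allowance for attrition: "With a 20% drop-out rate, sample size is estimated at 216 HCWs". No ICC, correlation over time or calculation method is given.

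Two other places bear on the figure. Under Informed consent and screening the article says: "If a participant withdraws after the baseline measures are completed, then no replacement is made". The Methods paragraph of the Abstract describes the HCWs as "grouped into 18 geographical clusters", which is not the number of clusters used in the Sample size section.

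**The concern.** The power statement needs 12 × 15 = 180 HCWs. The attrition sentence is there to set enrolment high enough that 180 remain after the assumed loss. The step from 180 to 216 adds 20% of the number needed, whereas a drop-out rate removes 20% of the number enrolled. The two operations do not cancel, so the enrolment figure falls short under its own assumption.

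This is the only HCW recruitment figure given for the primary outcome (SCIDS), and achieved enrolment and attrition will be judged against 216 and 20%. As written, the trial could meet both exactly and still miss the 180 on which its power statement rests. Because withdrawals after baseline are not replaced, recruitment would not make up the gap.

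**Working it through.** **Inputs from the Sample size section:** 12 clusters, 15 HCWs per cluster, 80% power, two-sided 5%, standardised effect 0.522, drop-out 20%, enrolment 216.

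**1. Reproducing 216.**
- Base: 12 × 15 = 180.
- n × (1 + d) = 180 × 1.2 = 216, an exact match. Per cluster, 15 × 1.2 = 18 and 12 × 18 = 216.
- n / (1 − d) = 180 / 0.8 = 225, which is not the stated figure. Per cluster, 15 / 0.8 = 18.75, rounded up to 19, and 12 × 19 = 228.

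**2. What 216 delivers.**
- Completers at 20% loss: 216 × 0.8 = 172.8, about 173, or 172.8 / 12 = 14.4 per cluster.
- Shortfall: 225 − 216 = 9 enrolled; 180 − 172.8 = 7.2 completers.
- Drop-out at which 216 still leaves 180: 1 − 180/216 = 16.7%.
- Check of the alternative: 225 × 0.8 = 180.

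Steps 1 and 2 need no assumption beyond the document's own figures.

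**3. Illustrative size of the effect on power (assumptions mine).** Take a parallel two-arm comparison of means, SD = 1, equal arms, a normal approximation, N HCWs in 12 clusters of m = N/12, and a design effect DE = 1 + (m − 1) × ICC. Then power ≈ Φ(0.522 × √(N / (4 × DE)) − 1.96).

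| Assumed ICC | Power, N = 180 | Power, N = 172.8 | Loss (points) |
|---|---|---|---|
| 0 | 93.8% | 92.9% | 0.9 |
| 0.01 | 90.7% | 89.7% | 1.0 |
| 0.02 | 87.2% | 86.1% | 1.0 |
| 0.04 | 80.1% | 79.1% | 1.0 |
| 0.05 | 76.6% | 75.6% | 1.0 |
| 0.10 | 61.8% | 61.1% | 0.7 |

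The loss is 0.7 to 1.0 points across the range. An ICC of about 0.04 happens to return the stated effect under this formula: (1.960 + 0.842) × √(2 × 1.56 / 90) = 0.522, where 1.56 = 1 + 14 × 0.04. That does not identify the sponsor's ICC. With a t reference distribution on 10 degrees of freedom (12 clusters less 2), an ICC of about 0.019 gives 80% power at 0.522, and an ICC of 0.04 gives about 71%.

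**4. The 18-cluster reading.** 18 × 12 = 216 as well. But the Sample size section mentions neither 18 clusters nor 12 HCWs per cluster; it ties 216 to the 20% rate immediately after "12 clusters with 15 HCWs per cluster". The match is a coincidence that the text does not use.

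**The case against.** The strongest reply is that the error does not matter. It concerns 9 people in a figure described as an estimate, in a study that began recruiting in June 2019 and was due to finish in April 2022. No design or analysis choice depends on it. This stands as to size, but it does not make the figure right.

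A reader might go further and infer that the trial is underpowered, with power of 79.1% or a detectable effect of 0.528 instead of 0.522. The documents do not support that, for four reasons.

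- Those two figures come from an ICC of 0.04 fitted backwards through one assumed formula. The article states no ICC and names no method.
- The formula is for a parallel trial, whereas the article describes a three-period stepped wedge with repeated measures on the same HCWs. A calculation for that design could give a different detectable effect, possibly a smaller one.
- The Statistics and data analysis section plans mixed models with random effects for cluster and participant, together with methods for missing data. HCWs who leave after baseline still contribute the periods they completed, so a loss of about 7 analysed HCWs is an upper bound.
- The cluster count is unsettled. If there are 18 clusters, as the Abstract says, 173 completers would give about 84% power under the same assumed formula and ICC of 0.04, which more than offsets the loss.

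None of this rescues 216 as an allowance for 20% drop-out. The plan itself chose to cover attrition by raising enrolment, and on that logic the inflation is wrong. Nor is this a detail left to a fuller document: it is a printed figure that disagrees with the printed rate beside it.

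**Conclusion.** The point holds as an arithmetic error in the drop-out allowance. The 216 HCWs do not return the 180 behind the power statement at the stated 20% loss; they return about 173. The matching enrolment is 225, or 228 with whole numbers per cluster, and 216 corresponds to a tolerated drop-out of 16.7%. That conclusion rests only on the document's own figures and on reading the rate as a proportion of those enrolled, which is the ordinary meaning.

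The consequence is small: about one point of power, illustrative, under an assumed parallel two-arm design-effect formula with ICC between 0 and 0.10. Part of that would be recovered by the planned mixed models. Whether the trial's actual power lies above or below 80% cannot be determined from the article. The difference between 12 and 18 clusters is a separate inconsistency, and it has to be settled before any restated power figure means anything.

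**What to change.** Correct the attrition sentence in one of two ways:

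- keep 216 and state that it allows for 16.7% drop-out, or that it leaves about 173 completers at 20%; or
- state 225 as the enrolment matching 180 completers at 20% drop-out (228 if rounded up to 19 in each of 12 clusters).

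With recruitment under way since June 2019, the first is the practical choice: it costs one sentence and no additional enrolment. The price is a slightly less favourable statement of what 216 provides.

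Do not insert a detectable effect or power figure derived from the illustrative calculation above. If the sponsor wishes to restate either, it should use its own ICC and method, after reconciling the 12 clusters in the Sample size section with the 18 in the Abstract.

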### Randomisation

HCWs are clustered according to the home care provider service region. Each cluster is randomly allocated to the study arms (the intervention or control groups) with block randomisation. The randomisation is conducted using online random number generators in the presence of an independent research staff member who is not employed in the study.

### Blinding

HCWs are unblinded during the study. The clients and family carers are told that their HCWs will receive the PITCH training but are not informed when training has occurred. Clients and family carers are not provided with information about the training content. HCWs are encouraged to not discuss the training with their clients.

Research staff liaising with the home care providers and the training team from the home care providers remain unblinded throughout the project. Research assistants collecting outcome measures during client, family carer, and HCW assessments are blinded to the randomisation condition.

### Statistics and data analysis

Baseline variables will be fully described using descriptive statistics. The primary (sense of competency) and secondary (dementia knowledge, attitudes, work strain) outcomes for HCWs will be analysed using linear mixed models or generalised linear mixed models (depending on the data distribution and extent of unequal cluster sizes). Secondary outcomes for clients living with dementia and family carers (social care, client experience, health-related quality of life, neuropsychiatric symptoms, disability, carer role strain, dyadic relationship) will be compared pre versus post intervention periods using linear mixed models or generalised linear mixed models. Time and intervention will be represented in these models as fixed effects, whilst cluster and participants will be represented as random effects.

All-cause client transition from the home will analysed using survival analysis, employing Cox proportional hazards modelling and Kaplan-Meier survival curves. Clients of HCWs who did and did not receive PITCH training will be compared using Log rank tests. A prospective economic evaluation will be used to inform the cost-effectiveness of the PITCH program. Incremental costs will be estimated relative to the controls. Quality of life measures will be used to estimate a quality-adjusted life year (QALY) profile for participants. This will be used to estimate the cost per QALY. Statistical uncertainty and sensitivity analyses will be included with these results. Intention-to-treat methods will be used to account for missing data. For missing data, based on the pattern of missingness, we will use either multiple imputation techniques, selection, or pattern mixture models, in consultation with a statistician.

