PITCH-trained HCWs will have an improved sense of competence in providing care, improved dementia knowledge, and reduced carer burden at 6 months, compared with HCWs not trained in PITCH.Clients of PITCH-trained HCWs will report a better experience with their home care service, improved quality of life and health, and exhibit fewer behaviours of concern at 6 months, compared with clients of HCWs not trained in PITCH.Family carers of clients of PITCH-trained HCWs will have reduced carer burden and reduced depressive symptoms at 6 months, compared with family carers of clients with HCWs not trained in PITCH.Clients with usual care will have fewer total days before an all-cause transition from the home event (such as admission to residential care) or greater client total number of transitions from home to hospital or other facilities, compared with clients of PITCH-trained HCWs.PITCH is effective compared to control in terms of quality-adjusted life years as measured by economic evaluation.

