#### Exclusion criteria

Clients: If (in the opinion of the service provider) their death is likely within the next 6 months due to the course of chronic disease (e.g. palliative), if they (or their family carers) have plans to move into an aged care facility within the next 6 months, or if they (or their family carers) have plans to change home care providers within the next 6 months.

Family carers: If they lack the ability to provide informed consent.

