### Secondary outcomes

HCWs will be assessed on their general knowledge of dementia using the Dementia Knowledge Assessment Scale (DKAS) [22]. Their attitudes towards people living with dementia will be assessed using the Dementia Attitudes Scale (DAS) [23], though the scale has been modified to change the term ‘ADRD’ (Alzheimer’s disease and related disorders) to ‘dementia’ for consistency with the other measures used. The stress experienced by HCWs in providing dementia care will be assessed using the Strain in Dementia Care Scale (SDCS) [24].

For clients living with dementia, their sense of control over daily personal life and social activities will be assessed by HCWs or family carers, using the Adult Social Care Outcomes Toolkit ASCOT-SCT4 [25]. Information about client experiences when receiving home care will be assessed using the Consumer Experience Report Pilot Draft (CER-Draft, new scale) [26]. The health-related quality of life of clients will be assessed using the Dementia Quality of Life (DEMQOL) [27] or proxy version (DEMQOL-Proxy). Family carers rate the presence and severity of client neuropsychiatric symptoms, as well as the level of caregiver distress resulting from the symptoms, using the Neuropsychiatric Inventory (NPI-12) [28]. Functional daily activities of people with dementia in community dwelling will be assessed using the Disability Assessment for Dementia Scale (DAD) [29]. Caregiver personal and role strain will be assessed by the family carer using the Zarit Burden Interview (ZBI) self-report scale [30].

By improving staff dementia knowledge, attitudes, confidence, and competence, it will likely improve the overall quality of dementia care provided by HCWs, with foreseeable client ability to remain independently living at home.

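### The hypothesised number of transitions from home has no planned analysis: only time-to-event methods are named, for an all-cause event that does not separate a temporary hospital stay from a permanent move

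*Protocol article*

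**What the plan says.** Three places in the protocol article bear on this outcome.

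- **Background, fourth hypothesis.** Clients under usual care are expected to have "fewer total days before an all-cause transition from the home event (such as admission to residential care) or greater client total number of transitions" than clients of PITCH-trained workers. The example given for the days part is residential care. The count part concerns a "greater client total number of transitions from home to hospital or other facilities".
- **Other outcomes.** One outcome is listed: "All-cause client transition from home will be collected from a variety of sources such as the case manager files, MBS and PBS data". Nothing says which moves count, whether a temporary stay counts, or how a permanent move is recognised.
- **Statistics and data analysis.** "All-cause client transition from the home will analysed using survival analysis, employing Cox proportional hazards modelling and Kaplan-Meier survival curves". Then: "Clients of HCWs who did and did not receive PITCH training will be compared using Log rank tests". No other method is given for transitions.

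The same section assigns linear or generalised linear mixed models to named outcomes. For workers these are competency, knowledge, attitudes and strain. For clients and carers they are social care, client experience, quality of life, neuropsychiatric symptoms, disability, role strain and the dyadic relationship. Transitions are not among them.

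**The concern.** A hypothesis about how many transitions a client has is not answered by a comparison of how long clients go before one. A Cox model in its usual form, Kaplan-Meier curves and a log-rank test use each client's first event and discard the rest. If PITCH reduced repeat hospital transfers without delaying the first one, the planned analysis would not show it.

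Two further points follow.

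- With an all-cause event, a night in hospital and a permanent move to residential care carry the same weight, although they mean different things for a client.
- The or in the hypothesis gives no order, so support could be claimed from whichever part turned out favourable.

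What is at stake is whether the trial can answer one of its own listed hypotheses. The primary result is not at stake.

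**Working it through.** **No figure to reproduce.** The article gives no event rate, hazard ratio or power for transitions. Its only power statement is for SCIDS.

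**Step 1. Match each part of the hypothesis to an analysis.**

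| Part of the hypothesis | Analysis named | Match |
|---|---|---|
| Days before an all-cause transition | Cox, Kaplan-Meier, log-rank | Yes |
| Total number of transitions to hospital or other facilities | None | No |

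**Step 2. What a first-event analysis records.** Three invented clients, all followed for 12 months, with hospital transfers counting as events:

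| Client | Course | First event | Transitions | Permanent move |
|---|---|---|---|---|
| A | One night in hospital in month 1, then home | Month 1 | 1 | None |
| B | Permanent move in month 10 | Month 10 | 1 | Month 10 |
| C | Hospital in months 1, 3 and 5, permanent move in month 8 | Month 1 | 4 | Month 8 |

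A and C are identical in the planned analysis, and A ranks worse than B. The count separates A from C. Time to permanent residential care orders all three: C, then B, then A with no move.

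**Step 3. How much could pooling matter? Illustration on assumed rates only.** Assume yearly risks of 10–30% for residential care and 20–60% for hospital, constant independent hazards, and no allowance for clustering. The article's figure of about 108 clients is split 54/54. The window is the first 6 months, before the control group is trained.

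- Hazard: h = −ln(1 − risk).
- Hospital share of first events in the control arm: hH / (hH + hR).
- All-cause hazard ratio if PITCH has a ratio of 0.6 on residential care and none on hospital: (0.6·hR + hH) / (hR + hH).

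| Residential risk | Hospital risk | hR | hH | Hospital share | All-cause ratio |
|---|---|---|---|---|---|
| 10% | 20% | 0.105 | 0.223 | 0.68 | 0.87 |
| 10% | 60% | 0.105 | 0.916 | 0.90 | 0.96 |
| 30% | 20% | 0.357 | 0.223 | 0.38 | 0.75 |
| 30% | 60% | 0.357 | 0.916 | 0.72 | 0.89 |

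On these assumptions the ratio of 0.6 appears as 0.75 to 0.96, and 5–20% of control-arm residential moves would follow a hospital transfer and so not be the first event. If PITCH instead has a ratio of 0.6 on both kinds of move, the all-cause ratio is (0.6·hR + 0.6·hH) / (hR + hH) = 0.6, and there is no dilution. The result therefore depends wholly on the assumptions.

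**Step 4. Information available.** On the same assumptions, both arms together give 4–14 residential moves and 15–49 first transitions of either kind in 6 months. With equal arms, the standard error of the log hazard ratio is about 2/√d for d events. For residential care, 4 events give 2/√4 = 1.00 and 14 events give 2/√14 = 0.53. A 95% interval then runs from the estimate divided by, to the estimate multiplied by, exp(1.96 × 1.00) = 7.1 or exp(1.96 × 0.535) = 2.9.

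**The case against.** **What stands.** No sentence says that a hospital transfer is an event in the survival analysis. Residential care is the example for the days part, and hospital appears in the count part. Strictly, the event is undefined, and pooling is only the natural reading of all-cause. Event definitions and permanence rules may sit in the full protocol or an analysis plan that is not shown. Nor does the article say that only the first event is used; a Cox model can be extended to recurrent events. All-cause time to transition is a legitimate composite, and it gains events if PITCH affects both kinds of move.

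**What it does not answer.** The article states a count hypothesis, then names the methods for transitions, and none of them as named estimates a count. That is a mismatch between two things the article does state, not a detail left for later. Resource use collected for costing does not supply a test of the number of transitions.

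**Stronger readings a reader might infer, which the article does not support:**

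- *A short hospital stay ends follow-up.* It would end time at risk for this one endpoint, if it counts as an event. The 6- and 12-month assessments continue.
- *A stated aim of staying at home goes untested.* The article describes this only as an expected benefit ("with foreseeable client ability to remain independently living at home"), and time to transition does bear on it.
- *The exclusion criteria remove residential moves from the first 6 months.* They exclude clients with "plans to move into an aged care facility within the next 6 months"; unplanned moves remain.
- *The composite mainly measures hospital admission and dilutes a PITCH effect by a known amount.* This needs event rates that the article does not give, and no PITCH effect on hospital admission. The Background says good home care reduces admissions as well as delaying institutionalisation.

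**Conclusion.** The point holds in a limited form. The hypothesised total number of transitions has no matching analysis; this follows from the text alone and needs no assumed rates. The second part, that a temporary hospital stay counts the same as a permanent move and that later transitions are not used, rests on the natural reading of all-cause and on the usual first-event form of the named methods.

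The size of any dilution cannot be derived from the article; the 0.75 to 0.96 range is an illustration and vanishes if PITCH affects both kinds of move equally. Replacing the all-cause composite outright would be a trade-off, because residential moves alone would be few. The matter is worth correcting because the change is small and lets the trial answer a hypothesis that it lists itself. It concerns an other outcome and leaves the primary SCIDS conclusion untouched.

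**What to change.** 1. **Keep** the all-cause time-to-event analysis, and state which moves count as a transition.
2. **Add a model for the number of transitions** to hospital or other facilities. One option is a negative binomial mixed model with the log of days at risk at home as offset and the same time, intervention and cluster terms as the other outcomes. A recurrent-event Cox model is another.
3. **Add a supportive analysis** of time to permanent residential care that is not ended by a temporary hospital stay, with death as a competing event and a rule for when a move is permanent.
4. **Replace the or** in the fourth hypothesis with a stated order, for example all-cause time first, number of transitions second, residential care as supportive.

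Cost: a few sentences in the plan and a little more analysis work. Transitions are already to be collected from case manager files and other sources. The article does not say that each transition's date and destination are recorded, so this should be confirmed. The downside is a wide interval for residential care, because events will be few among about 108 clients. That analysis should be reported as descriptive support, not as a test expected to be decisive.

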## Methods/design

### Trial design

This pragmatic stepped-wedge cluster-randomised controlled trial (SW-CRT) investigates the effectiveness of the PITCH training programme delivered to paid HCWs in improving their competency and dementia knowledge, overall family carers’ wellbeing and clients’ quality of life, and cost-effectiveness. The study participants are clients living with dementia, family carers, and HCWs.

Consistent with the stepped-wedge design, clusters of participants undertake PITCH training (the intervention) sequentially over time and, once their training is completed, will remain exposed to the intervention for the duration of the study. Every cluster begins in the control condition and eventually receives the intervention, with crossover determined randomly, ensuring eventual participation of all groups for ethical reasons. The study is conducted at six home care service providers, with each provider potentially contributing more than one cluster.

This SW-CRT is an interventional study for HCWs as they receive PITCH training, but a non-interventional study for the clients and family carers (no direct intervention treatment is given to clients). HCWs are randomly allocated to either the intervention groups that receive PITCH training at period 2 or the control groups that receives PITCH training at period 3. All participants are monitored throughout the SW-CRT and outcomes for all participants are assessed at three time periods: period 1 (baseline), period 2 (at 6 months), and period 3 (at 12 months). See Fig. 1.

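### Time to transition from home: the plan fixes Kaplan-Meier without saying how death at home is treated, and if such deaths are censored the curves overstate transition risk and days at home

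*Protocol article*

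**What the plan says.** The Statistics and data analysis section analyses transition from home by "employing Cox proportional hazards modelling and Kaplan-Meier survival curves", and adds: "Clients of HCWs who did and did not receive PITCH training will be compared using Log rank tests". No competing-risk method is named.

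The fourth hypothesis, at the end of the Background section, predicts that usual-care clients will have "fewer total days before an all-cause transition from the home event (such as admission to residential care"), or, as a separate alternative, a "greater client total number of transitions from home to hospital or other facilities".

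Other outcomes gives only the data sources: "All-cause client transition from home will be collected from a variety of sources such as the case manager files, MBS and PBS data". It contains no list of qualifying events and no rule for death.

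For clients, death is mentioned only under Exclusion criteria, which removes those for whom, in the service provider's opinion, "their death is likely within the next 6 months due to the course of chronic disease". Trial design sets assessments at baseline, 6 and 12 months, and the inclusion criteria admit dementia of any type and stage.

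**The concern.** A client who dies at home can no longer move to residential care. If transition alone is the event, death is a competing event, and a standard Kaplan-Meier analysis censors the client at death. The curve then describes a setting in which the dead would have stayed at risk of transition at the same rate as survivors. One minus that curve exceeds the proportion who actually transition, and days read from it include days after death.

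Some deaths should be expected: the population includes advanced dementia, and the exclusion looks ahead 6 months while follow-up runs for 12. The hypothesis is framed in days, and the Secondary outcomes section presents continued independent living at home as the hoped-for benefit. Time credited to clients who have died does not measure that benefit. A difference in deaths between groups would also not show in a curve for transition alone.

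**Working it through.** **What the text settles.** The estimator is fixed (Kaplan-Meier, Cox, log-rank) and so is the hypothesised quantity (days before transition). The status of death is not. The example in the days clause is residential care, and the count clause names hospital and other facilities. All are care settings, which favours reading the event as a move. The word *all-cause* and the open-ended example leave room for the other reading.

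**Inputs.** From the article: about 108 clients (Sample size), 12 months of follow-up (Trial design), and controls trained 6 months after baseline (Abstract, Methods). The article states no event rate for this outcome, so there is no planned figure to reproduce. Assumed: a 12-month transition risk of 40% on the censored scale; 12-month mortality at home of 5%, 10% or 15%; constant, independent hazards.

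**Formulas**, with *T* in years:
- a = −ln(1 − 0.40) = 0.5108; d = −ln(1 − mortality) = 0.0513, 0.1054, 0.1625
- One minus Kaplan-Meier, deaths censored: 1 − exp(−aT)
- True cumulative incidence of transition: a/(a+d) × [1 − exp(−(a+d)T)]
- Days from the censored curve: 365 × [1 − exp(−aT)]/a
- Days alive at home: 365 × [1 − exp(−(a+d)T)]/(a+d)

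**Worked case, 15% mortality, T = 1.** a + d = 0.6733 and exp(−0.6733) = 0.60 × 0.85 = 0.51.
- Cumulative incidence: 0.5108/0.6733 × 0.49 = 37.2%, against 40.0%
- Days alive at home: 365 × 0.49/0.6733 = 265.6, against 365 × 0.40/0.5108 = 285.8
- Deaths before transition: 108 × 0.1625/0.6733 × 0.49 = about 13

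**Results**

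| Horizon | Mortality (12-month) | 1 − KM | Cumulative incidence | Excess, points | KM days | Days alive at home | Excess, days |
|---|---|---|---|---|---|---|---|
| 12 months | 5% | 40.0% | 39.1% | 0.9 | 286 | 279 | 7 |
| 12 months | 10% | 40.0% | 38.1% | 1.9 | 286 | 272 | 13 |
| 12 months | 15% | 40.0% | 37.2% | 2.8 | 286 | 266 | 20 |
| 6 months | 5% | 22.5% | 22.3% | 0.3 | 161 | 159 | 2 |
| 6 months | 10% | 22.5% | 22.0% | 0.6 | 161 | 157 | 4 |
| 6 months | 15% | 22.5% | 21.7% | 0.9 | 161 | 155 | 6 |

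Excesses are taken before rounding.

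**Against sampling error.** The Greenwood standard error of the curve at 12 months is 0.60 × √{a[exp(a+d) − 1]/[n(a+d)]}. With n = 108 it is 4.8 to 4.9 points, so the excess in the proportion is 0.2, 0.4 and 0.6 standard errors. For one arm of 54 clients it is 0.1 to 0.4. These standard errors ignore clustering.

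**Sensitivity.** Over 12 months, with transition risks of 15–40% and mortality of 5–20%, the excess is 0.4 to 3.8 points and about 7 to 34 days. If death is an event, or nobody dies at home, it is zero.

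**Unequal deaths.** With a 40% transition risk in both groups and mortality of 15% against 10%, days alive at home over 12 months differ by 272 − 266, or about 7 before rounding. The censored curves show no difference. The standard error of a two-group difference with 54 clients each is about 23 days, so this is about 0.3 standard errors.

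**The case against.** The strongest reply is that the premise is not in the text. A reader might infer that the article excludes death from the event and censors clients who die. It says neither. An all-cause event with an open-ended example can be read to include death, and then Kaplan-Meier, Cox and log-rank are appropriate. A reader might also take the fourth hypothesis to give a closed list of residential care, hospital and other facilities. It does not: the hospital wording belongs to the separate clause on number of transitions. These points stand, and the finding is conditional for that reason.

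Second, a journal article condenses the full protocol, and a rule for death may sit there or in an analysis plan. That stands for the missing rule taken alone. It does not dispose of the point: the article fixes the estimator as well as the quantity, and a fuller document would have to count death in the event or move away from Kaplan-Meier for transition alone.

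Third, a reader might infer that the group comparison is invalid. It is not on this ground. With deaths censored, Cox and log-rank compare the rate of transition among clients still alive at home, which is a legitimate quantity. Kaplan-Meier is named only for curves and no restricted mean is planned, so the error in days arises only if days are read from the curve to answer the hypothesis.

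Fourth, size. Controls are trained at 6 months, so the 12-month figures overstate what affects the randomised contrast. The assumed mortality enters as death at home before any transition, so overall mortality would be too high an input. Both points stand.

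**Conclusion.** The point holds in conditional form. The article commits to Kaplan-Meier for transition from home and to a hypothesis in days, and leaves the status of death open. On the natural reading, where transition means a move to a care setting, deaths at home are censored and the curves overstate both transition risk and days at home. On the other reading there is no bias, but deaths would be reported as transitions and the outcome needs a truer name.

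The size is modest and rests wholly on assumed rates with constant, independent hazards: about 1 to 3 points and 7 to 20 days over 12 months, and under 1 point and about 2 to 6 days over the 6-month randomised contrast. Severity is low. The outcome is listed under Other outcomes, the relative comparison survives, and bias in a between-group difference in days depends on how deaths fall across the groups.

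**What to change.** In the Statistics and data analysis section:

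1. State whether death at home is an event, a censoring time or a competing event.
2. For the days hypothesis, analyse days alive at home, with the first of transition or death as the event, by Kaplan-Meier and Cox. Call it transition or death and show the two components.
3. For transition itself, replace Kaplan-Meier by the Aalen-Johansen cumulative incidence with death as a competing event. Report the cause-specific hazard ratio for transition beside the one for death.

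The cost is a few sentences and a few lines of code. Dates of death must be taken from provider or case manager files, which the study already uses. The drawback is that the composite mixes two different events, so it should not be reported without its components.
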